### Outcome Measures

The primary outcome is the time from randomization to hospital discharge within 30 days. Clinical decision to discharge an infant would usually follow national guidance. Secondary outcome measures are shown in **Table 2**.

**TABLE 2. T2:** Secondary Outcome Measures

**Outcome measure**
1) Proportion of infants experiencing treatment failure
2) Mortality at hospital discharge, day 30, and day 90
3) Proportion of infants requiring intubation and ventilation
4) Proportion of infants requiring admission to an ICU
5) Proportion of infants requiring sedation
6) Duration of oxygen therapy, defined as the time to being free from supplemental oxygen for > 4 hr
7) Time to adequate (75%) oral feeding
8) Time ready for hospital discharge, defined as the time from randomization to latest of time to being free of supplemental oxygen or adequate oral feeding
9) Patient comfort, assessed by the caregiver using the Face, Legs, Activity, Crying, and Consolability scale
10) Patient comfort, assessed by the parent/guardian using a visual analog scale
11) Proportion of infants requiring hospital readmission within 30 d
12) Health status at 30 and 90 d
13) Cost-effectiveness expressed in terms of incremental cost per quality-adjusted life year gained

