### Study Population and Screening

The study population will include hospitalized infants with acute bronchiolitis (**Table 1**). Eligible patients will be screened by clinical and research staff, for the severe stratum first, and if inclusion criteria are not met, for the moderate stratum. Fulfillment of any exclusion criteria will result in the patient being ineligible. Ineligible patients will be recorded on site screening and enrollment logs, explaining reasons for exclusion.

**TABLE 1. T1:** Eligibility Criteria for the Breathing Assistance in Children With Bronchiolitis (BACHb) Trial

**Inclusion criteria (severe bronchiolitis**)
Hospitalized infants < 12 mo old with a clinical diagnosis of acute bronchiolitis, clinically assessed twice at least 15 min apart to have:
severe respiratory distress (one or more of: respiratory rate > 70 breaths/min, grunting, marked chest recession) and/or
recurrent short apneas (> 3/hr, each apnea lasting < 10 s)
**Inclusion criteria (moderate bronchiolitis**)
Hospitalized infants < 12 mo old with a clinical diagnosis of acute bronchiolitis, clinically assessed twice at least 15 min apart to have a lack of response to low-flow oxygen (up to 2 L/min), as indicated by:
persistent hypoxemia (oxygen saturation < 90%, or < 92% if age < 6 wk or if underlying health problems present) and/or
moderate respiratory distress (respiratory rate 55–70/min and/or moderate chest recession)

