### Study Treatments

#### Humidified Standard Oxygen

HSO will be delivered as per usual practice at each site using either a headbox or facemask attached to a heater/humidifier. The gas flow rate will be titrated between 6 and 15 L/min to maintain oxygen saturations greater than 90% (or > 92% for infants < 6 wk old or children of any age with underlying health conditions) (27).

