#### High-Flow Nasal Cannula

HFNC will involve the delivery of heated, humidified gas through nasal cannula at the prescribed high-flow rate (2 L/kg/min). No specific device is recommended, and sites are expected to use their usual equipment.

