#### Continuous Positive Airway Pressure

CPAP may be delivered using any medically approved device that can provide an expiratory pressure of 6–8 cm H_2_O that is used as part of the site’s usual practice.

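### Secondary outcome 8 (time ready for hospital discharge) has no off-support condition, so an infant feeding in air but still on HFNC or CPAP counts as ready

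*Protocol article*

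**What the plan says.** The protocol article, Table 2 (Secondary Outcome Measures), defines three linked outcomes:

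- Item 6 reads: "Duration of oxygen therapy, defined as the time to being free from supplemental oxygen for > 4 hr".
- Item 7 reads: "Time to adequate (75%) oral feeding".
- Item 8 reads: "Time ready for hospital discharge, defined as the time from randomization to latest of time to being free of supplemental oxygen or adequate oral feeding".

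Under Study Treatments, the three modalities are specified in different terms:

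- HFNC by flow: "HFNC will involve the delivery of heated, humidified gas through nasal cannula at the prescribed high-flow rate", set at 2 L/kg/min.
- CPAP by pressure: "CPAP may be delivered using any medically approved device that can provide an expiratory pressure of 6–8 cm H_2_O".
- HSO by oxygenation: "The gas flow rate will be titrated between 6 and 15 L/min to maintain oxygen saturations greater than 90" percent, with a higher threshold for the youngest infants and those with underlying conditions.

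No oxygen fraction is stated for HFNC or CPAP. Table 1 lets infants enter the severe stratum without hypoxemia, because its first criterion is "severe respiratory distress (one or more of: respiratory rate > 70 breaths/min, grunting, marked chest recession) and/or"; the alternative criterion is repeated brief apnea. The moderate stratum also accepts distress alone, although every infant there has already been tried on low-flow oxygen.

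Secondary Outcomes Analysis says that time-to-event outcomes use the same Cox model as the primary outcome.

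**The concern.** Item 8 is printed as a complete definition, and it omits a condition that its name implies. An infant taking three quarters of feeds by mouth, in air, but still on HFNC or CPAP meets both stated conditions, yet is not ready to leave hospital.

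The omission would matter less if it fell equally on both arms, but the device is the randomized factor. In the moderate stratum, HSO is titrated to saturation, so the end of HSO and the end of oxygen largely coincide. HFNC runs at a set flow and can continue once no oxygen is added. The same recorded event can therefore mean off all support in one arm and still on the device in the other.

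What is at stake is how a secondary hazard ratio is read. The trial is open-label and its primary outcome depends on a clinical decision to discharge. Readers will naturally look to a criterion-based readiness time for support, although the article does not assign it that role.

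**Working it through.** **Which figures depend on item 8.** None that the article states. The required events concern time to actual discharge and reproduce without it:

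- Fixed design, 1:1, two-sided 5%, 90% power: events = 4(1.960 + 1.282)² / (ln HR)². This gives 845 at HR 1.25 and 517 at HR 1.33, rounded up.
- Four equally spaced looks with Lan-DeMets O'Brien-Fleming spending multiply this by 1.0183, giving 859.5 and 526.2. The article states 860 and 527.

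**When item 8 goes wrong.** For one infant let O be the time free of oxygen, F the time of adequate oral feeding and S the time off all support.

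- As written: R = max(O, F).
- With an off-support condition: R* = max(O, F, S).
- Error: R* − R = max(0, S − max(O, F)).

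The error is zero unless support ends after both oxygen and feeding are settled. Where feeding comes last, nothing is misdated. Where S is about equal to O, as is expected under HSO, the error is about zero. Under HFNC or CPAP, S can exceed O because neither is specified by oxygen fraction.

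**Direction.** Moderate stratum: errors can arise on HFNC and hardly at all on HSO, so readiness would tend to be dated too early on HFNC. Severe stratum: both HFNC and CPAP can run in air, so the sign depends on which arm has the longer interval, which the article does not say.

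**Size, as an illustration only.** The article gives neither the share of infants affected (q) nor the lag. Assumptions:

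- no true difference in R*;
- Weibull times with shape 1.5 and median 4 days;
- a share q of HFNC infants dated early by a fixed lag, and none in the comparator;
- 40,000 simulated infants per arm and a Cox hazard ratio for HFNC, divided by the hazard ratio with no misdating.

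| q | Lag 6 h | Lag 12 h | Lag 24 h |
|---|---|---|---|
| 0% | 1.00 | 1.00 | 1.00 |
| 10% | 1.01 | 1.01 | 1.02 |
| 25% | 1.02 | 1.03 | 1.06 |
| 50% | 1.03 | 1.07 | 1.13 |
| 100% | 1.07 | 1.14 | 1.30 |

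The corresponding shift in the HFNC median runs from 0.02 day (10%, 6 h) through 0.24 day (25%, 24 h) to 1.0 day (100%, 24 h).

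**The case against.** The strongest reply is that the state in question may be uncommon. An infant must be in air, taking 75% of feeds by mouth and still on the device, all at once. Whether that lasts for minutes or a day depends on the weaning algorithms in Figures 1 and 2, which are not available here. The full protocol or the SAP may already read freedom from oxygen as including freedom from the device. HSO infants who fail may also be switched to HFNC, and the treatment-policy strategy keeps them in their arm, which dilutes the contrast. All of this stands, and it limits what can be said about size. It does not change the printed rule: a weaning algorithm governs care and does not alter how an outcome is defined.

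Three stronger readings are tempting and are not supported.

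- A reader might infer that item 8 asks only for freedom from oxygen. It also requires feeding, which narrows the group at risk considerably.
- A reader might extend the criticism to item 6. That item is named and defined as duration of oxygen therapy and measures exactly that. It makes no claim about readiness.
- A reader might divide a 6 to 24 h lag by the one-day moderate-stratum target (a 20% reduction from a 5-day median) and report 25% to 100% of the effect. The lag is assumed, it applies only to the affected infants, and the target belongs to a different outcome, actual discharge.

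**Conclusion.** The point holds for item 8 alone. As printed, the definition can date an infant as ready for discharge while that infant is still on the randomized device. It can therefore bias the arm comparison, with a tendency to favour HFNC in the moderate stratum and no clear direction in the severe stratum. That the comparison is in fact biased is an inference the article does not support, because it shows neither how often support continues in air after feeding is established nor for how long.

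Under the assumptions above, the spurious hazard ratio is at most 1.06 when a quarter or fewer of HFNC infants are affected. It reaches about 1.30 only if every HFNC infant is misdated by a full day. If few infants feed on support in air, the effect is likely small. The conclusion about direction rests on HSO and oxygen stopping at about the same time, which follows from HSO being titrated to saturation but is not stated outright.

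One secondary outcome is affected. The primary outcome, the required events and the sample size use neither item 6 nor item 8, and nothing here bears on them.

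**What to change.** Define item 8 as the time from randomization to the latest of three events:

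- (a) free of supplemental oxygen, stating whether the four-hour requirement of item 6 applies, since item 8 does not repeat it;
- (b) off HFNC, CPAP, HSO and any higher respiratory support;
- (c) adequate oral feeding as in item 7.

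If the full protocol or SAP already includes (b), it is enough to say so wherever the outcome is described. Leave item 6 unchanged.

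No new data should be needed, because the abstract lists details of respiratory support among the data collected. The cost is a documented change to one secondary outcome in a trial that has been recruiting since October 2023. It should be dated, justified and fixed before arm-level results are seen, so that it cannot appear to be driven by the data. The present definition can be kept as a sensitivity analysis. The difference between the two versions would also show how many infants were affected and by how much.

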### Data Collection

Data will be collected and recorded using the electronic OpenClinica system, which is fully validated, records a full audit trail and includes a controlled access system. Sites will enter the required information into the system (**Fig. 3**), which will then be monitored by the Trial Monitor and Trial Manager, including the extraction of reports to monitor the trials progress.

**Figure 3. F3:**
[figure not shown]
Patient data collection schedule. CPAP = continuous positive airway pressure, FLACC = Face, Legs, Activity, Crying, and Consolability, HFNC = high-flow nasal cannula, HSO = humidified standard oxygen, IQI = Infant Quality of Life Instrument.

Data collection will include the completion of an Infant Quality of Life Instrument (IQI) questionnaire (33), the Pediatric Quality of Life Inventory and health economic questionnaires to monitor resource usage after discharge at 30 and 90 days post-randomization. These will be sent to parents through either post or electronically and will be entered onto the OpenClinica database.

### Statistical Methods

#### Sample Size

We assumed a median time to discharge of 5 days in the HSO group and 7 days in the CPAP group. The trial aims to detect a 20% reduction in HFNC compared with HSO in moderate bronchiolitis (hazard ratio [HR] = 1.25) and a 25% reduction compared with CPAP in severe bronchiolitis (HR = 1.33). To achieve 90% power at a 5% two-sided significance level, 860 events are required for the moderate group and 527 for the severe group.

Given the low competing risk of mortality (< 2%) and expected discharge within 30 days, we plan to recruit 462 infants per arm (moderate) and 292 per arm (severe), accounting for 7–9% censoring (death or hospital stay > 30 d) and consent refusals. Sample size calculations assume proportional hazards, four sequential tests with Lan-DeMets O’Brien-Fleming spending function. No multiple comparison adjustments are made, as the strata represent distinct treatment comparisons. Calculations were performed using rpact and validated with gsDesign3.3.0 (34, 35).

#### Clinical Effectiveness Analysis

All analyses will be lodged in a statistical analysis plan (SAP), a priori, before the first formal interim analysis. The trial results will be reported according to the Consolidated Standards of Reporting Trials extension for adaptive designs (36). The trial will consist of three formal interim analyses for efficacy when approximately 25%, 50%, and 75% of the planned number of events (hospital discharge) are available. The efficacy boundaries are computed using Lan-DeMets O’Brien-Fleming approximation symmetric efficacy boundaries (37), separately for each stratum (**Supplemental Table 1**, https://links.lww.com/PCC/C650). If the two strata hit the interim target at different time points, decisions for each stratum will be made separately. Statistical reports will be prepared within 1-month of hitting the interim targets. The Data Monitoring Committee (DMC) will review data at the interims and make recommendations to the TSC on whether there are any safety or efficacy reasons to stop the trial. None of the interim analysis results will be shared with the investigators before the completion of the trial.

#### Primary Estimand

The trial aims to determine whether first-line use of HFNC is superior to HSO and CPAP in reducing time to hospital discharge in moderate and severe bronchiolitis, respectively. The primary outcome of time to hospital discharge within 30 days will be measured as days between randomization and hospital discharge or date of last follow-up, whichever is earliest. Deaths will be censored at the time of death, with cause-specific HRs reported under a hypothetical approach for death as an intercurrent event (IE). Other IEs, including treatment escalation, switching, or not starting treatment, will be handled using a treatment policy strategy. Kaplan-Meier plots will display time to discharge distributions, and the Aalen-Johansen estimator will account for death as a competing risk. A cause-specific Cox proportional hazards model, adjusting for age and site, will estimate discharge rates, providing HRs with 95% CIs, with final *p* values judged based on the stage 4 boundary.

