#### Subgroup Analyses

Interaction effects between treatment and the following factors will be assessed: age groups, preterm infants (< 37 wk), prior bronchiolitis admission, underlying conditions, hospitals with on-site PICU, and respiratory syncitial virus (RSV) diagnosis. The study is not powered to detect interaction effects. Interaction effects will therefore be judged interesting with *p* values of less than 0.2.

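### The primary Cox model adjusts only for the stratification factors; adding three baseline factors already needed for the subgroup analyses could bring a modest gain in power

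*Protocol article*

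**What the plan says.** The Primary Estimand section of the protocol article names a cause-specific Cox model "adjusting for age and site". Under Randomization and Concealment, site and age (below or at least 6 weeks) are the two stratification factors, so the model adjusts for the stratifiers and nothing else.

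The Subgroup Analyses section lists further factors for treatment interactions, among them "preterm infants (< 37 wk), prior bronchiolitis admission, underlying conditions". The abstract says that baseline clinical characteristics are collected. The individual items are not listed in the text, and the data collection schedule (Figure 3) is not shown.

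The Sample Size section sets its target with "To achieve 90% power at a 5% two-sided significance level" and states that "860 events are required for the moderate group and 527 for the severe group". It makes no mention of covariates. The Clinical Effectiveness Analysis section describes three interim efficacy looks before the final analysis and says that the SAP is lodged before the first of them.

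**The concern.** Nearly all infants are expected to be discharged within 30 days. In a Cox model with so many observed events, leaving out a baseline factor that predicts the outcome pulls the treatment HR toward 1 and costs some power. Pre-specified adjustment keeps the type I error and guards against chance imbalance in factors that were not used for stratification. That protection matters most in the smaller severe stratum.

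The protocol itself suggests that one omitted factor may be prognostic. In Table 1 (moderate stratum) and in the description of humidified standard oxygen, infants with underlying health problems share the stricter saturation threshold with infants under 6 weeks. Table 2 ties readiness for discharge partly to being off supplemental oxygen. The protocol therefore treats young age and underlying conditions alike in this respect, but adjusts only for age. This makes an effect plausible without giving its size, and both places concern the moderate stratum. For preterm birth and prior admission the document offers no comparable pointer.

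At stake is a modest amount of precision that needs no extra infants and, as far as can be inferred, no new data items.

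**Working it through.** **1. The plan's own figures.** Inputs from the Sample Size section: two-sided 5%, 90% power, HR 1.25 (moderate) and 1.33 (severe), four looks with Lan-DeMets O'Brien-Fleming spending. The looks are at 25, 50, 75 and 100% of events.

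Fixed-design events (Schoenfeld, 1:1): D = 4(1.960 + 1.282)² / (ln HR)².

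- Moderate: 42.03 / 0.04979 = 844.1, so 845.
- Severe: 42.03 / 0.08133 = 516.8, so 517.

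Numerical recursion gives a four-look inflation factor of 1.0183 and a final boundary of z = 2.014.

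- Moderate: 844.1 × 1.0183 = 859.5, so 860.
- Severe: 516.8 × 1.0183 = 526.2, so 527.

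Both stated figures reproduce exactly, and power at these event counts is 90.0% in each stratum without covariate credit.

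**2. What the three factors could add.** The documents give no prevalence or prognostic effect, so this step rests on assumptions. Simulation: 2,500 trials per cell, 924 or 584 infants, exponential times, censoring at 30 days plus a small random loss, independent factors, and age under 6 weeks at 25% prevalence with a discharge HR of 0.75. A model with treatment and age group is compared with the same model plus the three factors. Site is not modelled, and there is one look at 1.96. The HRs 1.25 and 1.33 are taken as conditional on all covariates. Relative information is (mean Z with / mean Z without)².

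| Assumed effects | Prevalences | Discharge HRs | Relative information | Power, moderate stratum | Power, severe stratum |
|---|---|---|---|---|---|
| Weak | 15/10/10% | 0.85/0.80/0.90 | 1.02 | 91.6 → 91.8% | 91.7 → 92.2% |
| Moderate | 15/15/10% | 0.75/0.65/0.80 | 1.08 | 87.4 → 89.7% | 89.0 → 91.4% |
| Strong | 20/20/15% | 0.60/0.50/0.65 | 1.26–1.28 | 83.4 → 91.5% | 84.0 → 91.0% |

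The gain within a row is the result to use; the levels carry simulation error. In the middle row, moderate stratum, the adjusted HR was 1.249 with about 898 events. Then mean Z ≈ ln(1.249) × √(898/4) = 3.33, and power ≈ Φ(3.33 − 1.96) ≈ 91.5%. Without the factors, 3.33/√1.0776 = 3.21 gives about 89.4%. These levels lie about 2 points above the simulated ones, but the gain is the same, at about 2 points.

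**3. The same gain in the four-look design.** If 1.25 and 1.33 are instead the HRs under the age-and-site model, power at 860 and 527 events starts at 90.0%. It becomes about 90.6% with information × 1.02, and about 92% with × 1.08 (91.4% at × 1.05, 92.5% at × 1.10). With × 1.20 to × 1.30 it is 94.5 to 95.9%. If the factors are not prognostic, it stays at 90.0%.

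**4. Change of target.** The HR is non-collapsible, so the extended model estimates a slightly different conditional HR. In the moderate stratum the average estimate moves from 1.238 to 1.249 under moderate effects and from 1.22 to 1.25 under strong ones.

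**The case against.** Adjusting for the stratification factors alone is standard, and the plan reaches its power without more. That stands, and it is why this is not an error.

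A reader might infer that the trial is underpowered as planned, for example from the 87.4% or 83.4% above. The documents do not support this. Those levels arise because the simulation fixes 1.25 as conditional on the extra factors. The protocol ties it to a 20% reduction from a control median of 5 days and does not define it that way. Read as the HR under the planned model, nothing is lost against plan.

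A reader might also take a larger gain from comparing the full model with a Cox model that has no covariates. That is the wrong comparator, since age and site are already in the model.

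Listing a factor for an interaction test does not declare it prognostic, so the two sections do not contradict each other. The subgroup list shows only that the data must exist. Even that is inferred, though the inference is strong for underlying conditions, which the hypoxemia criterion in Table 1 requires. The other two listed factors are poorer candidates: an on-site PICU is a property of the site, and the article does not say whether RSV status is known at randomization.

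Two practical objections hold. The smaller model is simpler and avoids missing covariates. Changing the model after an efficacy look would alter the test statistic partway through the sequence, and the boundaries would no longer follow automatically. Covariate-adjusted sensitivity analyses may also stand in the SAP, which is not shown, so their absence from the article is no finding. The primary covariate set, however, is stated in the article and can be judged.

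**Conclusion.** The point holds as a missed efficiency of modest size. Under weak to moderate assumed effects, adding the three factors raises effective information by about 2 to 8%, or roughly 0 to 2.5 points of power, in either stratum. Gains of about 5 to 8 points need discharge HRs of 0.50 to 0.65, for which the documents give no support. If the factors are not prognostic, the gain is near zero, and three extra terms cost almost nothing against 860 and 527 events.

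The size rests on assumed prevalences and effects, independent factors and exponential times. The direction does not depend on these choices as long as the factors are prognostic to some degree.

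**What to change.** In each stratum, pre-specify preterm birth (below 37 weeks), underlying condition and prior bronchiolitis admission as fixed effects in the primary Cox model, alongside age group and site. Handle site as already planned. Decide this before any unblinded comparative analysis of that stratum and without reference to interim results. Use the same model at every look, state a simple rule for missing baseline values, and keep the age-and-site model as a sensitivity analysis.

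The article does not say whether an interim look has taken place. If one has been done in a stratum, keep the age-and-site model as primary for the sequential boundaries there and report the extended model as a pre-specified sensitivity analysis.

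The change costs protocol and SAP wording and no additional infants. The price is a slightly more complex model, the missing-covariate rule, and a conditional HR that differs slightly from the one under age and site alone, which the estimand text should state.
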